# Three-dimensional corrective exercise therapy for idiopathic scoliosis: study protocol for a prospective non-randomized trial

**DOI:** 10.1186/s12891-022-05057-7

**Published:** 2022-02-05

**Keywords:** Idiopathic scoliosis, Three-dimensional corrective exercise, Cobb angle, Physical conditions, Quality of life

## Abstract

**Background:**

Although physiotherapeutic scoliosis-specific exercises (PSSEs) with or without other conservative treatments may improve scoliotic deformities, the evidence is insufficient. Three-dimensional corrective exercises (TDCEs) for scoliosis are based on the theory of PSSEs and are characterized by a combination of outpatient treatment and home-based exercise. This study aims to evaluate the effectiveness of TDCEs for idiopathic scoliosis (IS).

**Methods:**

The participants will be divided into two age- and sex-matched groups: an experimental group (EG) treated with three-dimensional corrective exercise therapy (TDCET) and a control group (CG) receiving generalized exercise therapy. In each arm, mild and moderate IS cases will be reclassified based on the Cobb angle and biopsy results. The primary endpoint is the change in the largest Cobb angle; the secondary endpoints are the sagittal index, forced vital capacity, peak oxygen uptake, and peak oxygen uptake. Sixty-six patients with mild IS and 78 patients with moderate IS will be included.

**Discussion:**

This study is the first controlled trial to systematically assess the effectiveness of TDCEs for IS. In addition to TDCET including three-dimensional corrective exercises, family rehabilitation and basic body awareness therapy may help patients adopt supportive attitudes and appropriate behaviours, thus enhancing their compliance with exercises and achieving better outcomes.

**Trial registration:**

The study protocol was registered at www.clinicaltrials.gov (number identifier: NCT04539522). Registered on August 27, 2020.

**Supplementary Information:**

The online version contains supplementary material available at 10.1186/s12891-022-05057-7.

## Background

Scoliosis is defined by a lateral curvature of the spine (Cobb angle) of at least 10 degrees observed through anteroposterior direct radiography, and this curvature is typically associated with trunk rotation [1]. Idiopathic scoliosis (IS) is the most common clinical entity with an unclear aetiology, and overall prevalence has been reported to be 0.47–5.2% in the current literature [2]. Almost 10% of individuals with adolescent idiopathic scoliosis (AIS) require some form of treatment, and as many as 0.1% curvatures progress to a Cobb angle exceeding 45–50° may eventually require surgery [3]. In addition to the physical implications of IS such as postural changes, an altered appearance, pain, respiratory symptoms and cardiopulmonary dysfunction [4–6], research has shown that this patient group can experience other issues that affect quality of life and lead to psychosocial difficulties [1], including restricted social participation with increased psychiatric consultations, and these patients have been associated with higher rates of eating disorders and suicide [7].

A spinal curvature exceeding 30° is considered a risk factor for health disorders in adulthood [8]; therefore, scoliosis-related scientific societies (i.e., the Scoliosis Research Society [SRS] and the International Society on Scoliosis Orthopaedic and Rehabilitation Treatment [SOSORT]) set a 30° Cobb angle as the best achievable goal for conservative treatments, which includes observation, physiotherapeutic scoliosis-specific exercises (PSSEs), and bracing [9].

Some experts propose PSSEs as compensatory strategies with bracing to prevent potential adverse effects on the muscles and spine as well as to increase brace effectiveness. Moreover, PSSEs can be used as a stand-alone treatment with milder curves to avoid bracing. The latest review concluded that insufficient evidence is available to suggest that PSSEs with or without other conservative treatments can reduce the Cobb angle and improve trunk appearance and balance, [10] and three other reviews of studies conducted between 2005 and 2020 suggested that the few clinical trials on the effects of PSSEs on scoliotic deformities that exist are of low quality [11–13]. Surprisingly, Cantele et al. affirmed that quality of life and self-perception can be impaired in scoliotic girls, especially when they practise PSSEs, because PSSEs are often perceived by adolescents as stressful, boring and limiting to other everyday activities, even when specific exercise programmes may help prevent scoliosis curve progression and improve their health and fitness status when routinely performed [14].

Three-dimensional corrective exercises (TDCEs) for scoliosis are based on the theory of PSSEs and are characterized by the combination of outpatient treatment and home-based exercise: 1) the outpatient treatment component includes three-dimensional self-correction, stabilization of the corrected posture, stretching, manual fascia relaxation therapy, and breathing training, and 2) the home-based exercise component includes active self-correcting exercises combined with basic body awareness therapy. However, according to data from previous randomized controlled trials (RCTs) regarding exercise or bracing, RCTs are not very feasible because of ethical reasons and the high rate of families refused randomization and stated preference for one treatment over the other [15, 16]. Ferriter et al. reported that a non-randomized controlled trial (non-RCT) of high quality can produce outcomes that approximate those found in RCTs [17]. Therefore, a non-RCT was designed to test the following hypothesis: TDCEs are effective in patients with either mild or moderate IS.

This quasi-experimental prospective longitudinal trial aims to evaluate the effectiveness of a 6-month TDCEs programme versus a control programme for IS. Physical conditions and quality of life will be measured before and after the 12-month intervention to quantify changes and treatment effects. Furthermore, the rehabilitation process will be assessed carefully regarding goal setting and attainment. The flow diagram is shown in Fig. 1.

**Fig. 1 Fig1:**
[figure not shown]
SPIRIT figure

## Methods/design

Approval and registration of the study is confirmed. The design of this clinical trial follows the recommendations of the SPIRIT guidelines (2013). The conditions described lay a solid foundation for the feasibility of this trial. The trial was registered prospectively at www.clinicaltrials.gov (NCT04539522).

### Participants and setting

We will recruit 144 Patients from the outpatient clinic of the Rehabilitation Department in Xinhua Hospital in the Shanghai Jiao Tong University School of Medicine, Shanghai, China. The department is one of the first scoliosis rehabilitation centres in Shanghai, and the clinicians have a great deal of experience treating IS using conventional methods, especially with regard to exercise therapy. Annually, approximately 1000 IS outpatients visit the department, and approximately 200 of them receive outpatient treatment 1–3 times a week. In addition, the paediatric outpatient department is open for 12 h per day, which is convenient for patients. The conditions described lay a solid foundation for the feasibility of this trial.

### Participant recruitment

Both mild and moderate IS patients from the outpatient clinic will be recruited and stratified by disease severity. Experienced clinicians will divide the participates who meet the inclusion criteria into mild or moderate subgroups according to Cobb angle on the anteroposterior and lateral whole-spine X-rays in the standing position taken at the first visit. Written informed consent will be obtained from participants who meet all the inclusion and none of the exclusion criteria and the parents. Then, participants will be assigned to two age- and sex-matched groups. No further recruitment measures will be taken, and no individuals with a direct relationship with the researchers, such as students/staff of the hospital or close relatives, will be included. Patient enrolment started in November 2020 and is scheduled to end in December 2021.

### Eligibility criteria

Participants must meet all of the following criteria for inclusion:IS with a Cobb angle greater than or equal to 10 degrees and less than 45 degreesAged between 8 and 16 years old

Cobb angles of less than and greater than 25 degrees on the anteroposterior and lateral whole-spine X-rays taken in the standing position are classified as mild and moderate scoliosis, respectively, according to the SOSORT guidelines.Mild IS is defined as a Cobb angle of not less than 10 degrees but less than 25 degreesModerate IS is defined as a Cobb angle of not lower than 25 degrees but less than 45 degrees

### Exclusion criteria

Participants will be excluded if they meet one of the following criteria:An age < 8 years or > 16 yearsScoliosis caused by congenital, postural, neuromuscular or other diseases (such as neurofibromatosis, Marfan syndrome, bone dysplasia, metabolic or endocrine diseases, etc.)The apical vertebrae being located at T7 or aboveA history of pulmonary, cardiovascular, myo-articular, or neurological diseasesA history of cognitive and/or physical impairments that would preclude the patient from performing either the exercise therapy or the tests for the study’s outcome measuresA history of rehabilitation or surgery before the first visitComplete ossification of the entire growth plate

### Participant timeline

We adhered to the Standard Protocol: Recommendations for Interventional Testing (SPIRIT) in the development and reporting of our protocol (Fig. 1) [18].

**Fig. 2 Fig2:**
[figure not shown]
Timeline of the study

#### Three-dimensional corrective exercise therapy

TDCET is a series of exercises based on the theory of PSSEs and consists of two parts (Fig. 3):1) integrated outpatient treatment, including manual fascia relaxation therapy, stretching, three-dimensional self-correction exercises based on the pathological mechanics of IS (including longitudinal stretching and pelvic adjustments in the coronal plane to correct the lateral curvature, physical exercises for the sagittal profile to improve thoracic spinal extension range of motion, and exercises with a wedge pad to modify the “humpback” posture, and horizontal trunk and pelvic rotations) and breathing training, and 2) family rehabilitation, which includes self-correcting exercises and basic body awareness therapy to learn the correct postures that need to be adopted in everyday life activities. The participants in the exercise group will perform 60-min integrated outpatient treatment 1–3 times a week under the guidance of a physical therapist in an outpatient clinic and 40-min family rehabilitation per day under the supervision of the parents at home. In addition, the parents will send the exercise records to the physiotherapist through the Micro Message Public Platform.

**Fig. 3 Fig3:**
[figure not shown]
The content of TDCET

#### Generalized exercise

The participants in the CG will perform generalized exercise (GE) for a 60-min period 1–3 times a week under the guidance of a physical therapist in an outpatient clinic and 40-min self-correcting exercises per day under the supervision of the parents at home and the exercise records will also be sent to the physiotherapist through the Platform. CE will consist of a series of low-impact stretching and strengthening activities, such as curl-up, dead bug, side bridge, and birddog exercises [19].

#### Bracing

For all moderate IS patients, the Chêneau brace will be worn for not less than 22 h a day. The treatment regimen will last for 12 months.

### Incompliance or termination of the allocated intervention

Any subject who does not follow or complete the intervention period as specified in the protocol will be considered an incompliant subject.

The following are possible reasons for incompliance or termination:Poor intervention compliance will be considered if the level of compliance to the treatments in the outpatient clinic is less than 80%. Compliance = (total number of outpatient treatments/minimum required number) × 100%.Patients who consume drugs or participate in interventions that are not permitted during the clinical study, including other hormones (e.g., somatotropic hormone) and therapies (e.g., chiropractic and osteopathy) not mentioned in the trial, will not continue the study.Patients with incomplete information due to a failure to complete the entire course of treatment for any reason will not continue the study.Patients in whom scoliosis progresses at a rapid pace and surgery is recommended will not continue the study.Patients with accidental injuries (such as sprains, fractures, and traumatic injuries) making it inappropriate to continue the trial and need to discontinue treatment will not continue the study.

The following measures should be taken:An attempt to contact the subject should be made to ask for an explanation for incompliance or termination, and the results of the last assessment should be recorded.For patients who need to withdraw from testing due to anaphylaxis, adverse reactions, or treatment failure, appropriate treatment measures should be taken immediately.A form should be completed to explain the reason for study termination or incompliance.Intention-to-treat (ITT) analyses will be performed for incompliant patients, as appropriate. If the incompliance rate exceeds 10%, the reason for incompliance will be explained in detail.

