### Outcome measures

The study will be conducted over a period of 12 months. All outcomes will be assessed at baseline and after the 12-month intervention. In total, one primary outcome indicator and four secondary outcome indicators will be analysed:The primary outcome indicator is the change in the largest Cobb angle.

It is recommended that the magnitudes of the scoliotic curves are measured using the Cobb method. The Cobb angle will be measured on the standing frontal radiograph according to the Cobb method by a physician specializing in the treatment of scoliosis.2)The secondary outcome measures will be as follows:The sagittal index (SI) is the sum of the plumbline distances at C7 and L3. When SI<60 mm, the back is considered flat; 60–95 mm is in the normal range; and > 95 mm is considered kyphosis [20].Forced vital capacity (FVC) is an established measure of pulmonary function.Peak oxygen uptake (VO_2_peak) is recognized as the best expression of exercise endurance and will be measured by cardiopulmonary exercise testing.Quality of life will be evaluated by the Scoliosis Research Society-22 (SRS-22) questionnaire. This questionnaire was specifically designed for patients with scoliosis and consists of 22 items addressing 5 dimensions: function/activity, pain, self-image, mental health, and satisfaction with treatment. The higher the score is, the better the outcome.

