### Statistical analysis

All statistical procedures will be performed according to the principles of intention-to-treat (ITT). Outcome assessor will be blinded after assignment to interventions. A linear mixed model will be used to identify the differences between the TDCET group and the CE group in the change of the largest Cobb angle, SI, FVC, VO_2_peak and SRS-22 questionnaire scores across the periods of assessment (intervention factors and time) in the mild and moderate subgroups. The Risser sign will be considered a covariate. When necessary, post hoc comparisons will be performed using the Bonferroni correction for multiple comparisons. The correlations between the clinical variables (Cobb angle) and secondary variables (SI, FVC, VO_2_peak and SRS-22 questionnaire scores) will be assessed. All data will be analysed using SPSS v.23.0 software. *P* < 0.05 will be considered statistically significant.

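### Children who leave the study, some because of their primary outcome, have no planned 12-month Cobb angle, so the promised intention-to-treat analysis becomes in effect a completers' analysis

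*Protocol article*

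**What the plan says.** The section on incompliance or termination lists who leaves:

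- Progression: "Patients in whom scoliosis progresses at a rapid pace and surgery is recommended will not continue the study".
- Non-completion: "Patients with incomplete information due to a failure to complete the entire course of treatment for any reason will not continue the study".
- Other treatment: the same consequence applies to "Patients who consume drugs or participate in interventions that are not permitted during the clinical study", and to children whose accidental injury makes continuing inappropriate.

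For these children the section asks for an attempt at contact, a form giving the reason, and that "the results of the last assessment should be recorded". It then adds: "Intention-to-treat (ITT) analyses will be performed for incompliant patients, as appropriate".

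Under Outcome measures, "The primary outcome indicator is the change in the largest Cobb angle", and the timing is: "All outcomes will be assessed at baseline and after the 12-month intervention". The Statistical analysis section states: "All statistical procedures will be performed according to the principles of intention-to-treat (ITT". It names a linear mixed model, fitted within the mild and moderate subgroups, with intervention and time as factors.

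**The concern.** Rapid progression that leads to a surgery recommendation lies at the bad end of the primary endpoint, yet it is a reason for leaving the study. Non-completion and the use of other therapies may also be related to how the curve is doing. If leavers have no follow-up value, missingness depends partly on the outcome and may differ between arms.

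The bias could go either way. If the control arm loses more of its worst results, the estimated benefit shrinks. If children doing badly on TDCET leave more often, it grows. In neither case does the estimate describe everyone assigned. Groups here are formed by matching on age and sex, not by randomization, so this selection comes on top of whatever confounding is already present.

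**Working it through.** **1. Is a follow-up value planned for leavers?** The removal rules end study participation, and the outcome schedule has two points, baseline and 12 months. A child who leaves in between has no further scheduled assessment.

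- For most leavers the last scheduled assessment is therefore baseline, which gives no change.
- A child referred to surgery must have had a later radiograph, because progression cannot be seen from baseline alone. But no section makes that radiograph the outcome value.

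**2. Are the two intention-to-treat statements compatible?** The Statistical analysis section applies the principle to every procedure. The incompliance section applies it to incompliant patients only with a closing qualifier that leaves the decision open. The two cannot both govern the same children.

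**3. Does the mixed model recover the lost information?** The check simulated the moderate stratum with 39 per group, SD 3.75, true difference 2.82, a random intercept, and baseline-only records for children above a cut-off that removes 10% of controls (100 replicates). Mean estimated differences were:

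- mixed model: 2.34
- completers only: 2.35
- all children measured: 2.95

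The last figure differs from 2.82 by simulation error: the standard error is 3.75 × √(2/39) / √100 = 0.085. A child with only a baseline value adds almost nothing to the estimated change.

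**4. What does the sample-size allowance cover?** The plan's inflation reproduces: 26/0.8 = 32.5, rounded up to 33 (mild), and 31/0.8 = 38.75, rounded up to 39 (moderate). This replaces lost numbers. It does not correct loss that depends on the outcome.

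**5. How large could the surgery-progression rule be?**

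From the Sample size section: moderate SD 3.75 and difference 2.82; mild SD 7.48 and difference 6.1. The strata are 25 to below 45 degrees and 10 to below 25 degrees (Eligibility criteria). The Background section associates curves beyond 45–50 degrees with possible surgery.

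Assumed, not in the documents: normal changes, control mean +1 degree, baseline uniform within the stratum, and removal when a child worsens by more than 5 degrees and also ends above Z, with Z = 45 or 50.

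For baseline b the cut-off is t(b) = max(5, Z − b), and a(b) = (t(b) − μ)/σ. Averaging over b, the fraction removed is p = mean of [1 − Φ(a)], and the removed part of the mean is E = mean of [μ(1 − Φ(a)) + σφ(a)]. The mean among those kept is (μ − E)/(1 − p).

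Moderate stratum (μ = +1 for control, 1 − 2.82 = −1.82 for TDCET):

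| Z | Removed, control / TDCET | Mean kept, control / TDCET | Difference | Loss |
|---|---|---|---|---|
| 45 | about 5% / 1.1% | +0.67 / −1.92 | 2.59 | (2.82 − 2.59)/2.82 = 8% |
| 50 | 1.4% / 0.3% | +0.90 / −1.84 | 2.74 | (2.82 − 2.74)/2.82 = 3% |

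Mild stratum (μ = +1 and 1 − 6.1 = −5.1): under 0.1% of controls are removed, and the loss is under 1%.

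**6. What could the non-completion rule add?** No rate is given. As an extreme, suppose one arm loses only its worst fraction f. With z the upper-f normal point, that arm's mean shifts by σφ(z)/(1 − f):

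- f = 5%: 3.75 × 0.103/0.95 = 0.41 degrees
- f = 10%: 3.75 × 0.1755/0.90 = 0.73 degrees

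The apparent benefit falls by that amount if the control arm loses these children, and rises by it if the TDCET arm does.

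**The case against.** Several objections limit this point.

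- **Who is removed.** A reader might infer that every rapidly progressing child leaves. The rule requires a surgery recommendation as well, so a child who worsens without one stays in. Children below 80% outpatient compliance are labelled incompliant but are not expressly removed.
- **Size.** Removing every moderate-stratum child who worsens by more than 5 or 6 degrees would, under the same normal model, give 2.13 or 2.32 instead of 2.82, a loss of 25% or 18%. No section sets such a cut-off, so those figures do not describe the stated rule. The 20% allowance covers loss from all causes and does not show how many children would leave for progression.
- **Zero change.** A reader might infer that children referred to surgery would be scored as unchanged from baseline. A later radiograph must exist for them, and recording the last assessment may capture it. Carrying values forward is mentioned nowhere.
- **Missing detail.** That no 12-month radiograph is taken from leavers is an inference. The text plans none but forbids none, and the section title speaks of terminating the intervention. The handling of missing data and any sensitivity analyses may sit in a full protocol or SAP that is not shown.

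The first three objections stand, and the conclusion is limited accordingly. The fourth stands for the choice of analysis method. It does not remove the contradiction in the printed text: the stated consequence is leaving the study, and the two intention-to-treat statements differ. Nor can an analysis plan recover radiographs that were never taken.

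**Conclusion.** The concern holds. Followed as written, the removal rules and the two-visit schedule leave no planned 12-month Cobb angle for leavers, some of whom leave because of the primary outcome. The analysis is then in effect one of completers, contrary to the intention-to-treat promise.

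The direction of bias is not fixed, and the documents do not give its size. The 3% to 8% loss from the surgery-progression rule in the moderate stratum rests on the assumed normal changes, control mean, uniform baseline and surgical zone. The same rule matters very little in the mild stratum. Non-completion for any reason is potentially the larger source, in either direction, but its rate is unknown, and the 0.41 and 0.73 degree shifts are extremes for the fractions assumed.

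**What to change.** 1. In the incompliance section, separate stopping the programme from leaving outcome follow-up. When treatment stops is not at issue and stays as it is.
2. Seek the 12-month Cobb angle from every assigned child who still consents, whatever the reason for stopping.
3. For children referred to surgery, name the radiograph on which the recommendation was made as the source of the outcome value.
4. Delete the qualifier that closes the intention-to-treat sentence in the incompliance section, and reconcile that section with Outcome measures and Statistical analysis.

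The sample size does not change and no new type of examination is needed. The cost is wording, some follow-up effort, and some outcome values that date from before 12 months. The change has to be made while follow-up is open, because values not collected then cannot be recovered.
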